### **Hypotheses**

This protocol is hypothesis-supporting and hypothesis-testing.

#### **Primary Hypothesis:**

1. Participants allocated to adaptive therapy will show significantly higher biochemically confirmed 30-day continuous abstinence at 12 weeks post TQD.

#### **Secondary Hypotheses:**

2. Participants allocated to adaptive vs standard treatment will show significantly higher biochemically confirmed 7-day point prevalence abstinence at 2 and 12 post TQD assessment visits.
3. Participants allocated to adaptive vs standard treatment will show significantly higher phone-assessed self-reported abstinence at 1, 2, 6, 12, 26, and 52 weeks post-TQD.
4. Participants allocated to adaptive vs standard treatment will show lower number of cigarettes per day (cpd) at 2- and 12-weeks post TQD.
5. Participants allocated to adaptive vs standard treatment will show lower number of cigarettes per day (cpd) on phone-based self-report at 1, 2, 6, 12, 26, and 52 weeks post-TQD.

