#### Secondary Objectives

2. To compare 7-day point prevalence biochemically confirmed abstinence rates at 2- and 12-weeks post-TQD in participants randomized to adaptive vs standard treatment.
3. To compare phone-assessed self-reported abstinence at 1, 2, 6, 12, 26 and 52 weeks post-TQD in participants randomized to adaptive vs standard treatment. Phone assessments will be compared at specific time points and also across multiple time points using multi-level modeling.
4. To compare smoking reduction (number of cigarettes per day) at 2 and 12 weeks post TQD in participants randomized to adaptive vs standard treatment.
5. To compare smoking reduction (number of cigarettes per day) on phone-based self-report at 1, 2, 6, 12, 26, and 52 weeks post-TQD in participants randomized to adaptive vs. standard treatment. Phone assessments will be compared at specific time points and also across multiple time points using multi-level modeling.

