### 13.4 Statistical Hypothesis, Model, and Method of Analysis

Outcomes will be analyzed using generalized linear regression modeling using an ANOVA-based design; randomization status to both pharmacotherapy and behavioral groups will be denoted using a proxy variable to test primary study effects. An alpha criterion of 0.05 (two-tailed) will be used in all comparisons.

**Data Management and Statistical Procedures:** All data measures collected during study visits (e.g., smoking history, demographics, standardized tests on nicotine dependence, anxiety, stress etc.) will be captured in the EMR. Phone-based data will be captured using REDCap, an encrypted, HIPAA compliant, Duke Translational Medicine Institute (DTMI)-based data collection system allowing for multi-site data entry, direct participant electronic data upload through interface with computer terminals or tablets, time-based data entry (for use in calendar-based Assessment Visits) and capacity for direct upload into statistical programs SAS, SPSS, R, Excel for analysis. Trained staff (Duke CITI certification) will conduct data integrity processes for REDCap data with download into SAS (SAS Institute, Cary NC).

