**Analysis of Primary Outcome:** The primary outcome measure is biochemically confirmed 30-day continuous abstinence at the 12-week post-Target Quit Day (TQD) confirmed by carbon monoxide (CO) breath testing with CO < 7ppm. The study hypothesis is that adaptive treatment arms of the study will show higher smoking abstinence at 12-weeks post-quit attempt vs. non-adaptive treatment. An intent-to-treat approach will be taken to analyze primary outcomes such that all subjects who are enrolled in the study will be included in the primary analysis of outcomes. Outcomes will be analyzed using generalized linear regression modeling using an ANOVA-based design. An alpha criterion of 0.05 (two-tailed) will be used in all comparisons. For a conservative estimation of abstinence, subjects lost to follow-up after the point of randomization will be counted as non-abstinent. Following this, however, a sensitivity analysis will be conducted to determine the impact of this assumption, using multiple imputation procedures that model smoking outcomes in terms of “missingness” and smoking at previously observed time-points.

**Secondary smoking outcomes:** Analysis of secondary smoking outcomes will include comparison of abstinence rates in Adaptive vs. Non-Adaptive groups via self-reported 7 and 30-day continuous abstinence and number of cigarettes smoked per day at 2- and 12-weeks post TQD. Secondary smoking outcomes will be assessed using intent-to-treat principles with use of multiple imputation to account for missing data.

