### 13.4 Sample Size Calculation

**Outcomes:** The primary outcome for this study is biochemically confirmed 30-day continuous smoking abstinence at 12 weeks post TQD across all enrolled participants (intent-to-treat). Secondary outcomes include smoking abstinence at other time points (2 week visit), smoking reduction from baseline to follow-up visits, assessment of baseline variables as potential moderators of smoking behavior, assessment of psychological variables as potential mediators of smoking behavior, and assessment of economic outcomes. The sample size for this study was calculated based on effect sizes from prior studies on Varenicline and nicotine patch. Abstinence within these two arms will be assessed as secondary outcomes and are not expected to reach significance on all secondary outcomes. The study is powered to reach significance on the primary outcome (abstinence across the two arms combined).

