**Varenicline-Based Treatment (secondary outcome):** Power calculation for Varenicline Based Adaptive treatment vs. Varenicline Standard Treatment is based on abstinence rates observed in prior P50-funded trials as well as other published studies. To estimate the effect of adaptive treatment, a critical consideration is that 4 week Varenicline pre-cessation treatment without adaptation was superior to starting 1 week prior to quit day (Hajek et al 2011). Abstinence rate were 20.8% 1-week pre-quit start time. Hajek further showed that for participants starting 4 weeks prior to the Quit day, 35.4% of participants showed >50% reduction in cigs/day with an abstinence rate of 66.7% whereas 64.6% of participants failed to show >50% reduction in cigs/day and had an abstinence rate of 22.6%. The weighted average of these groups = 38.2%. Sample size calculation using **38.2% vs. 20.8%** with 2-tail test with continuity correction assuming  $p = 0.05$  and power = 80%, yields a minimum sample size of **208** within the Varenicline arm alone. This study is designed with 150 in the Varenicline arm and so it underpowered to reach this secondary outcome.

Version Date: 02/26/2020

**Full Sample (Primary Outcome):** Based on these calculations, a sample size of 300 for each of these comparisons should be sufficient to demonstrate significant differences between randomized arms (150 vs. 150). The Primary Outcome is a comparison of 12-week post-TQD smoking abstinence across the study sample (N=300). As stated above, the nicotine patch arm will require n=298 to reach significance, and the varenicline arm will require n=208 to reach significance. Neither arm (150 each) is powered to reach significance. The two arms together (n=300) are powered to reach primary outcomes. For the control group (nicotine patch arm = 26.0%; varenicline arm = 20.8%), an equally weighted sample would result in an abstinence rate of **23.4%**. For the adaptive treatment group (nicotine patch arm = 41.2%; varenicline arm = 38.2%), an equally weighted sample would result in abstinence rate of **39.7%**. A sample size calculation using 2-tail test with continuity correction assuming  $p = 0.05$  and power = 80% results in sample size of **248**. With 300 participants this study as power of 87% power for showing significant results on our primary outcome.

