## Appendix 11: Recent Smoking

*The follow questions are about your recent smoking*

1. In the last 7 days, have you smoked at all - even a puff?  
1=YES  
2 = No  
0 = Don't know
2. In the last 7 days, how many cigarettes have you smoked per **day**?  
  
\_\_\_\_\_ [0-99]
3. In the last 30 days, have you smoked at all- even a puff?  
1= YES  
2 = No
4. On average, how many cigarettes have you smoked per day over the last 30 days?  
\_\_\_\_\_

**Adherence questions- These questions will be used for phone-based assessments. Medication adherence for in-person visits will be assessed via diaries, which is found in Appendix 20.**

(CTA Dialogue)

Medications that have been given to you for this study should be taken as follows

- Patch: put on in AM and wear for 24 hours unless otherwise directed
- Study pills: are each taken two times per day, in the morning and in the evening unless otherwise directed by study personnel

1. Did you choose to use the nicotine patch or varenicline?

1= Nicotine Patch

2= Varenicline

If "Nicotine Patch" selected ,go to questions 1a-1c.

If “Varenicline” selected, go to questions 2a-2c

1a) Over the last seven days, how many days have you used the nicotine patch as prescribed?

1b) Over the last seven days, how many days have you used the pills as prescribed?

1c) If answer to 1a or 1 b is less than 7 (100% adherence), please provide reason why you did not follow the directions above.

2a) Over the last seven days, how many days have you taken the varenicline pills as prescribed above?

2b) Over the last seven days, how many days have you taken the bupropion pills as prescribed above?

2c) If answer to 2a or 2b is less than 7 (100% adherence), please provide reason why you did not follow the directions above.

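### The cigarettes-per-day secondaries are defined in three different ways and name no baseline adjustment; one definition with screening cpd as a fixed covariate would settle this at almost no cost

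*Protocol*

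**What the plan says.** The same two secondary items are described in three ways.

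- **Reduction.** Section 3.1, Secondary Objectives, item 4 reads "To compare smoking reduction (number of cigarettes per day) at 2 and 12 weeks post TQD". Item 5 says the same for the phone calls, and Section 13.2 repeats both. Section 13.4 (Sample Size Calculation) lists "smoking reduction from baseline to follow-up visits" among the secondary outcomes.
- **Level at the time point.** Secondary hypothesis 4 in Section 3.1 says adaptive participants "will show lower number of cigarettes per day (cpd) at 2- and 12-weeks post TQD", and hypothesis 5 does the same for the calls. Section 3.6 and the paragraph on secondary smoking outcomes in Section 13.4 (Statistical Hypothesis, Model, and Method of Analysis) also name the level, in the latter as "number of cigarettes smoked per day at 2- and 12-weeks post TQD".
- **Abstinence.** In the Section 6 table, the endpoint entered against both cpd objectives is self-reported abstinence, not a cigarette count.

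On the model, Section 13.4 says "Outcomes will be analyzed using generalized linear regression modeling using an ANOVA-based design". The only model term it names is randomization status. For the phone data, Sections 3.1 and 13.2 add a multilevel model. The one covariate rule (Section 6, first exploratory row) covers demographic variables, applies to abstinence outcomes and depends on significance. Smoking heaviness appears in Sections 3.6 and 13.5.1 only as a possible predictor or moderator of abstinence.

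Baseline cpd is available. Section 10.1 collects the smoking history and recent smoking questionnaires at screening, before randomization. Appendix 2 asks for average cpd. Appendix 11 asks "In the last 7 days, how many cigarettes have you smoked per" day, and has a 30-day version.

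**The concern.** An analyst working from this text could report cpd at the visit, absolute change, percent reduction or an abstinence proportion, and each could be defended from some passage. Section 13.4 also says "An alpha criterion of 0.05 (two-tailed) will be used in all comparisons". With two clinic visits and six phone time points, an open definition leaves room to choose the form after seeing the results.

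Precision is also at stake. Without baseline cpd in the model, an analysis of level ignores what baseline says about later smoking. An analysis of change subtracts the whole baseline value, which over-corrects when the correlation is modest. Adjustment avoids both and uses data that the trial already holds.

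**Working it through.** **The plan's own figure.** The protocol gives no sample size or power figure for cpd. Its figures concern the primary abstinence outcome: 248 in total for 39.7% vs 23.4%, and "With 300 participants this study as power of 87% power for showing significant results on our primary outcome". The unpooled normal formula without continuity correction reproduces them:

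- n per arm = (1.960 + 0.842)² × (0.397 × 0.603 + 0.234 × 0.766) / 0.163² ≈ 124, so 248 in total
- power at 150 per arm = 87.0%

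The text names a continuity correction; with it the total is 278 and power about 83%. That is a separate matter. Nothing below alters these figures.

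**Inputs for cpd.** From the protocol: 150 per arm and two-sided alpha 0.05. Assumed, because the protocol is silent: equal SDs at baseline and follow-up, correlation ρ from 0.1 to 0.7, and an illustrative true difference of 0.3 SD.

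**How the estimates relate.** Let D be the arm difference in mean cpd at follow-up, B the chance arm difference in mean baseline cpd, and β the slope of follow-up on baseline.

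- Level: D
- Absolute change: D − B
- Baseline-adjusted (ANCOVA): D − βB

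Randomization makes B zero on average, so all three have the same expectation. In one trial, level and change differ by B. Its standard error is √(2/150) = 0.115 baseline SD, so a gap beyond 1.96 × 0.115 = 0.23 SD arises about 5% of the time.

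**Level and change coincide after adjustment.** If Y − X = a + bT + cX, then Y = a + bT + (c + 1)X. The treatment coefficient b is identical. This needs an identity link.

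**Variances, in units of SD².** Level: 1. Change: 2(1 − ρ). ANCOVA: 1 − ρ². The saving from ANCOVA is therefore ρ² against level and 1 − (1 + ρ)/2 = (1 − ρ)/2 against change. The smallest difference detectable with 80% power is (1.960 + 0.842) × √(2v/150), where v is the variance.

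| ρ | Saving vs level | Saving vs change | Detectable difference in SD: level / change / ANCOVA | Power at 0.3 SD: level / change / ANCOVA |
|---|---|---|---|---|
| 0.1 | 1% | 45% | 0.323 / 0.434 / 0.322 | 74% / 49% / 74% |
| 0.3 | 9% | 35% | 0.323 / 0.383 / 0.309 | 74% / 59% / 78% |
| 0.5 | 25% | 25% | 0.323 / 0.323 / 0.280 | 74% / 74% / 85% |
| 0.7 | 49% | 15% | 0.323 / 0.251 / 0.231 | 74% / 92% / 95% |

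Below ρ = 0.5 change is the weaker of the two unadjusted forms; above it, level is. At ρ = 0.3 the choice between these two wordings moves power by 15 points.

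**If the SDs differ.** Var(change) = σ_Y²(1 − ρ²) + (σ_X − ρσ_Y)². The first term is the ANCOVA variance and the second cannot be negative. So the direction of the result does not depend on equal SDs, but the percentages do.

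**Percent reduction.** This divides each person's change by that person's own baseline, so a cigarette counts for more in a light smoker. It is not a rescaling of the arm difference in mean cpd, and the identity above does not cover it.

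**The case against.** The strongest reply is that most of this is drafting. Level and absolute change share one expected arm difference, so neither is biased. Both analysis summaries (Sections 3.6 and 13.4) already name the level. Covariates for a secondary outcome are commonly left to the statistical analysis plan, which is not at hand. All of that stands, but it does not remove the conflict: the objectives, the sample size section and the endpoint table say something else, and no passage says which governs.

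A reader might infer that the trial will analyse cpd by ANOVA without baseline cpd. The documents do not support that. A generalized linear regression can carry a baseline term, and none is excluded. For item 5 the multilevel model of Section 13.4 also allows person-level variables, and Appendix 19 asks 7-day cpd at every call from the first, one day after enrollment. Later pre-quit calls fall after the adaptive arms have begun active treatment, so they cannot serve as baseline.

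A reader might also infer that the loss of precision is known to be large, or that participants could be saved. Neither follows. The protocol gives no correlation, and a low one is plausible when many follow-up values are zero; at ρ = 0.1 the gain over level is 1%. The total of 300 is set by the primary outcome.

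Finally, adjustment makes level and change agree only with an identity link. With a log link, which the word generalized permits, they would not. That is a reason to fix the outcome as the level and to state the link.

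**Conclusion.** The point holds as an inconsistent definition of two secondary endpoints, together with a cheap improvement in method. The firm part needs no assumption: three outcomes are named for the same objectives, and no baseline adjustment is specified although baseline cpd is collected.

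It would be too strong to call level and absolute change different estimands. They are two estimators of one effect that differ in precision and, through chance baseline imbalance, in the estimate and p-value. The ambiguity reaches the estimand only if reduction means percent reduction. The protocol does not say so for these items, though its responder rule (Section 10.2) does measure reduction in percent. The abstinence wording in Section 6 is a different outcome altogether.

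The size of the precision gain rests on assumed equal SDs and ρ from 0.1 to 0.7: 1% to 49% against level and, over the same range, 45% to 15% against change. The change is worth making because it costs so little. The primary outcome, the sample size and the stated power are not affected.

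**What to change.** 1. Define the outcome for items 4 and 5 once, as cpd at each time point. Bring the objectives and hypotheses in Section 3.1, the Section 6 endpoint entries, Section 13.2 and both sections numbered 13.4 into line. The Section 6 entry for item 5 also leaves out week 12, which the objective includes.
2. Name one screening item as baseline cpd. The 7-day item in Appendix 11 fits best, because the visit diary and the phone item asked at every call also cover 7 days.
3. State in Section 13.4 that baseline cpd enters as a fixed covariate, chosen in advance and not by significance, in the linear model for each time point and in the multilevel model. State the identity link, and use robust standard errors because many values will be zero.
4. Add that, under this model, absolute reduction and level give the same arm difference. If percent reduction is wanted as well, label it as a separate outcome.

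The cost is a few lines of text, matched in the statistical analysis plan. It needs no new data, visit or participant.

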#### **Exploratory Objectives**

6. The following baseline self-report assessment outcomes will predict biochemically confirmed 30-day continuous abstinence at 12 weeks post TQD and 7-day point prevalence abstinence at 2- and 12-weeks post-quit: nicotine dependence, depression, anxiety, stress, alcohol use, drug use, motivation, and self-efficacy.
7. The following baseline self-report assessment outcomes will predict lower number of cpd and higher number of days abstinent at 2- and 12- week visits: urge, withdrawal symptoms, depression, anxiety, stress, alcohol use, drug use, motivation, and self-efficacy.
8. The following baseline self-report assessment outcomes will predict abstinence on phone-based self-report at 1, 2, 6, 12, 26, and 52 weeks post-TQD urges, withdrawal, motivation to quit smoking or remain abstinent, and confidence in ability to quit or remain abstinent
9. Baseline scores on anxiety, depression, and stress will moderate the effect of allocation to Non-Responder status in the adaptive and standard treatment arms. This finding will show that poor response to pharmacotherapy may be related to high levels of anxiety, depression, or stress.
10. A prospective economic analysis of adaptive vs standard treatment will show cost-benefit outcomes from the perspective of people that smoke cigarettes, healthcare systems, insurance companies, and employers.
11. **Feasibility:** Demographics of patients at DSCP and Duke CSC will reflect the recruitment area
12. **Feasibility:** Medications used will show wide variation of use.
13. **Feasibility:** Attendance at DSCP Return Appointments will be favorable.
14. **Feasibility:** Referral Routes to DSCP will reflect recruitment area.
15. **Feasibility:** Medication side effects will be favorable.
16. **Feasibility:** Medication adherence will be favorable.

## **3.2 Background and Significance**

**Adaptive Treatment Regimens:** The primary study treatment is a medication strategy referred to here as the adaptive pharmacotherapy algorithm. This strategy uses FDA-approved medications for smoking cessation (Varenicline, Nicotine Patch and Bupropion). Two weeks after starting these treatments, participants are assessed to see how much they have reduced their smoking on these medications. If, after 2 weeks of treatment, participants have reduced their cpd to 50% or less of baseline, they are considered to be “responsive” to treatment and are continued on this treatment alone until 12 weeks post-TQD. After 2 weeks of treatment, participants who have not decreased their cigarette use to 50% or more of their baseline cpd are considered “non-responders”, and Bupropion is added to the treatment regimen 2 weeks prior to the quit attempt and continued until 12 weeks post TQD. Estimates based on prior studies within our lab (see preliminary studies) suggest 50% will be non-responders.

**Pharmacotherapy Control:** The control group used for this algorithm is Varenicline started 1 week prior to TQD (1 week escalating dose) or Nicotine Patch started on the TQD and continuing to 12 weeks post-TQD. This is considered standard of care treatment. P-Varenicline and P-Patch for control participants only will be started 4 weeks prior to TQD, and P-Bupropion will be started 1 week prior to TQD to match study groups

**Behavioral Treatments:** All participants will receive one 40-minute visit with a medical provider who specializes in tobacco dependence treatment.

**Rationale for Research:** The primary disease population is people that smoke cigarettes, with the goal of decreasing the incidence of cancer and other smoking-related illnesses. Smokers are at significantly increased risk of multiple forms of cancer (USDHHS, 2014). The unmet need of this treatment is that current methods used to treat smokers yield low abstinence rates. Smoking is the number one cause of preventable morbidity and mortality in the US, claiming over 500,000 lives per year (USDHHS, 2014). There is currently compelling evidence from our research center (Duke Center for Smoking Cessation) and from other investigators that adaptive treatment of smokers who fail to respond to Varenicline or Nicotine patch alone will lead to higher abstinence rates than Varenicline used in usual dosing protocols (see below). If the adaptive approach is found to be effective, it might be implemented as a treatment strategy by clinicians.

## **Existing Evidence for Intervention**

**A. Use of Adaptive Pharmacotherapy Algorithm:** Trials have shown that a number of pharmacotherapies are effective for smoking cessation including Bupropion, Nicotine Lozenge, and Nicotine Patch and have found even greater effectiveness for combination nicotine therapy and Varenicline (Mills et al., 2012; Piper et al., 2009). Today, however, there is growing evidence that pharmacotherapies might be more effective if they are tailored to specific patients based on their early response to a treatment regimen (Pancani et al., 2015). Preliminary studies at Duke University have demonstrated a simple method to provide “targeted therapy” to smokers through an adaptive pharmacotherapy algorithm, referred to throughout this protocol as the “Algorithm” (Rose, 2011; Rose & Behm, 2013, 2014; Rose, Herskovic, Behm, & Westman, 2009). Algorithm-based treatment results show two patterns of response. Responders (smokers who decrease their cigarette use by 50% or more during the pre-quit treatment) show high-level abstinence rates using only the medication on which they were started (see preliminary studies below). Non-Responders (smokers who do not show a 50% decrease in cigarette use during the pre-quit treatment) show much lower abstinence rates overall (see below) with Patch or Varenicline but show significant increases in abstinence rates with the addition of Bupropion. In this study, we will provide non-responders with Bupropion as an “adaptive treatment” with the goal of improving abstinence rates in these individuals.

**B. Use of Behavioral Therapies:** It is now well established that the use of pharmacotherapies and behavioral therapies together result in higher abstinence rates than either approach alone (Alterman, Gariti, & Mulvaney, 2001; Evins et al., 2001; Fiore, 2008; Whitlock, Orleans, Pender, & Allan, 2002). Meta-analyses across multiple interventions show that the effectiveness of behavioral therapy is robustly related to treatment intensity and overall time commitment (Fiore, 2008; Stead & Lancaster, 2012). In accordance with these findings, the study will utilize a single 40-minute treatment with encouragement, quit day planning, discussion of prior quit attempts, and smoking triggers.

**C. Economic Assessment:** Economic analyses have found smoking cessation interventions to be highly cost-effective when compared to conventional standards of quality-adjusted life year saved (QALYs), including sub-populations of older smokers, pregnant women, and racial/ethnic minorities (Barnett et al., 2014; Cooper et al., 2014; Dornelas et al., 2006; Gordon, Graves, Hawkes, & Eakin, 2007; Ronckers, Groot, & Ament, 2005; Ruger & Lazar, 2012; Ruger, Weinstein, Hammond, Kearney, & Emmons, 2008). There is growing evidence that the financial gains to employers from employee smoking cessation may make employer-based cost incentives cost-effective to both employers and employees (Berman, Crane, Seiber, & Munur, 2014; Bunn, Stave, Downs, Alvir, & Dirani, 2006; Burton et al., 2005; Giles, Robalino, McColl, Sniehotta, & Adams, 2014; Halpern, Shikhar, Rentz, & Khan, 2001). With development of new treatment strategies, there is a growing need for studies testing the economic impact of outcomes in healthcare systems (Papadakis et al., 2014). The proposed study includes an economic analysis of adaptive treatment vs. standard pharmacotherapy.

